#### Secondary outcomes

We will conduct exploratory analyses on the secondary outcomes (PPA, TUG test and Short Performance Physical Battery). Given that a potential source of bias in this trial will result from patients being unblinded to their group allocation, group will be controlled for in all secondary analyses.

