#### Falls prevention clinic visit

The measurements listed below are acquired as part of the Falls Prevention Clinic visit and will be collected as the participants' baseline values upon informed consent.

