### Randomization

Participants will be randomly assigned (1:1) to either the OEP (plus standard of care) group or the standard of care (control) group. The randomization sequence will be stratified by: 1) sex, as falls rate is different between men and women; and 2) geriatrician (LD and WC), as standard of care delivery may differ between physicians. Permuted blocks of varying size (for example, 2,4,6) will be employed. To ensure concealment of the treatment allocation, the randomization sequences will be generated and held by a central Internet randomization service.

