#### Primary outcome

The rate of falls (the primary outcome) will be compared between the two groups using a negative binomial regression model. The treatment assignment and stratification factors will be included in the model as covariates. Point and interval estimates for the rate ratio will be determined.

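### Controlling for group in the secondary analyses cannot deal with bias from unblinded participants, because group is the treatment contrast

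*Protocol article*

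**What the plan says.** The Secondary outcomes section of the protocol article opens: "We will conduct exploratory analyses on the secondary outcomes (PPA, TUG test and Short Performance Physical Battery". It then names a potential source of bias and gives the response to it in the same sentence: "patients being unblinded to their group allocation, group will be controlled for in all secondary analyses". It names no model for these outcomes and no other covariate.

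Elsewhere the article makes clear what group is. Under Randomization: "Participants will be randomly assigned (1:1) to either the OEP (plus standard of care) group or the standard of care (control) group". Under Primary outcome, for the falls model: "The treatment assignment and stratification factors will be included in the model as covariates".

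Baseline PPA, TUG and SPPB are available. Under Falls prevention clinic visit: "The measurements listed below are acquired as part of the Falls Prevention Clinic visit", and these serve as the participants' "baseline values upon informed consent". The Measurements section sets sessions at baseline, 6 months and 12 months. Under Participants, the research assistant who does the baseline assessment stays blinded to allocation. The article does not say who assesses at 6 and 12 months.

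**The concern.** The sentence links a bias to a remedy, and the remedy cannot act on the bias. Adjustment works for a variable that differs from the exposure and accounts for part of the outcome. Here the proposed control variable is the exposure itself. A participant's knowledge of the arm is fully aligned with the arm, so its effect on effort, behaviour or test performance is counted as treatment effect.

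At stake is what will be said about these comparisons. TUG and SPPB depend partly on effort, and PPA includes performance tests, so knowledge of allocation could plausibly shift them. If the sentence is carried into the results paper, a between-group difference may be presented as having been protected against this bias when it was not.

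**Working it through.** The plan gives no figure on this point, so there is none to reproduce. The check is one of logic, with a simulation as illustration.

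**Step 1: what the group coefficient estimates.** Let g = 1 for OEP and 0 for control, let τ be the true treatment effect, and let b be the mean shift in the OEP arm that arises only because participants know their allocation. Then

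E(Y | g) = μ + g·τ + g·b = μ + g·(τ + b).

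The data identify only the sum τ + b. A model with g in it returns τ + b. The bias removed is b − b = 0, for any b.

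**Step 2: illustration.** From the Power calculation section: 172 participants per group. Assumed, because the article does not give them: τ = 0; b = 0, 0.2 or 0.3 SD; baseline-to-follow-up correlation r = 0.5 or 0.7; two-sided 5% level. Each setting used 4000 simulated trials fitted by least squares, first with group only, then with group plus the baseline value.

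| r | b | Group only: estimate | Rejected | With baseline: estimate | Rejected | Variance ratio |
|---|---|---|---|---|---|---|
| 0.5 | 0 | 0.003 | 4.8% | 0.003 | 5.1% | 0.77 |
| 0.5 | 0.2 | 0.199 | 45.1% | 0.200 | 56.1% | 0.76 |
| 0.5 | 0.3 | 0.301 | 79.8% | 0.301 | 89.5% | 0.74 |
| 0.7 | 0 | -0.001 | 4.5% | 0.001 | 5.3% | 0.53 |
| 0.7 | 0.2 | 0.198 | 45.0% | 0.198 | 72.5% | 0.53 |
| 0.7 | 0.3 | 0.295 | 77.6% | 0.299 | 96.8% | 0.51 |

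A hand check agrees. The standard error with group only is √(2/172) = 0.108 SD, so a shift of 0.2 SD gives z = 0.2/0.108 = 1.85, just short of 1.96, and a rejection rate a little under one half.

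With group in the model the whole shift is returned as an apparent effect. Adding the baseline value leaves it in place. Because the standard error is smaller, the biased result is declared significant more often.

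**Step 3: what baseline adjustment does offer.** Against an unadjusted comparison of final values, the variance ratio is 1 − r². Against change scores, whose variance is 2(1 − r) in the same units, the ratio is (1 − r²)/[2(1 − r)] = (1 + r)/2.

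| Assumed r | Against final values, 1 − r² | Against change scores, (1 + r)/2 |
|---|---|---|
| 0.6 | 0.64 | 0.80 |
| 0.7 | 0.51 | 0.85 |
| 0.8 | 0.36 | 0.90 |

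The gain is real in both cases. Its size depends on a correlation and a comparator that the article does not give.

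**The case against.** The strongest defence is that the sentence does little harm. Group belongs in the secondary model anyway, so removing the faulty reason changes no estimate, interval or p-value. The analyses are labelled exploratory, and the falls analysis is specified separately. The three outcomes are measured performance tests rather than self-reports, which leaves little room for reporting bias, although effort effects remain possible. The sentence also names participant unblinding openly as a potential source of bias and does not say that the bias is eliminated. All of this stands and limits the severity. It does not rescue the reasoning: a wrong property is stated, and no covariate list in an unseen analysis plan could make it true.

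A reader might infer that the baseline values will go unused, since only group is named. The documents do not support that. This is a condensed article that gives no model for these outcomes, and a covariate list for exploratory analyses is commonly left to the full protocol or the analysis plan. For the same reason, one cannot claim that the planned analysis wastes a known share of the sample. Correlations of 0.6 to 0.8 would correspond to 1/0.64 = 1.6 to 1/0.36 = 2.8 times the sample size, but only with those assumed correlations and against an unadjusted comparison of final values that the article never states. Against change scores the factor would be 1/0.80 = 1.25 to 1/0.90 = 1.11.

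It is also tempting to say that a blinded assessor solves the problem. Assessor blinding limits detection bias. It does not remove the effect of participants' own knowledge, which is the bias that the section names.

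**Conclusion.** The point holds as one of stated rationale. Controlling for group removes none of the bias from participants knowing their allocation. This result is exact and rests on no assumed figure; the simulated estimates and false-positive rates do rest on the assumed shifts and correlations and are illustrations only. The document gives no means of estimating how large the unblinding shift might be, so it cannot be said that the secondary results will be materially biased.

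Baseline adjustment is a worthwhile improvement to write in when the sentence is replaced. Its absence from the article is not an established defect, and its gain cannot be quantified from the documents.

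Severity is minor to moderate. A reader might take this as a flaw that must be cured before the trial can be interpreted, but the outcomes are exploratory and the primary falls comparison is untouched.

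**What to change.** In the Secondary outcomes section:

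- Delete the statement that group is controlled for because participants are unblinded. State instead that the group coefficient is the estimated treatment effect.
- State that this effect is estimated for PPA, TUG and SPPB in a model that adjusts for the baseline value of that outcome and for the stratification factors, sex and geriatrician. Give the purpose as precision and correction of chance imbalance, not control of unblinding bias.
- Name participant unblinding as a remaining limitation of these comparisons.
- State that the blinded research assistant does the 6- and 12-month assessments, if that is the arrangement, and say that this limits detection bias only.

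The cost is wording. The baseline values and stratification factors are already collected, and neither the sample size nor the visit schedule changes. If the analysis plan already specifies the baseline covariates, only the rationale and the two statements on blinding need to change.

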#### Economic evaluation

Our economic evaluation will examine the incremental costs and benefits generated by using the OEP intervention versus standard of care. The outcome of our cost effectiveness analysis is the incremental cost-effective ratio (ICER). By definition, an ICER is the difference between the mean costs of providing the competing interventions divided by the difference in effectiveness, where ICER = ∆cost/∆effect [62]. Both a cost-effectiveness analysis and a cost utility analysis will be performed. Based on the primary outcome of the RCT, we will determine the incremental cost of the OEP intervention per fall avoided, relative to standard treatment. We will also conduct a cost-utility analysis. In a cost-utility analysis, the primary outcome is the quality-adjusted life years. These are calculated based on the quality of life of a patient (measured using health utilities) in a given health state and the time spent in that health state. An important aspect of economic evaluations conducted alongside an RCT is how to deal with missing data due to attrition. We will follow recommendations by Oostenbrick and colleagues [63] and Briggs and colleagues [64], and the International Society for Pharmacoeconomics and Outcomes Research [65], in dealing with missing cost and effectiveness data. We will use a combination of imputation and bootstrapping to quantify uncertainty due to missing values.

#### Mediation analysis

We will use path analysis – a special case of structural equation modeling where all variables are observed – to investigate how physiological function and cognitive function mediate the effect of the intervention on the primary outcome (that is, falls). Using Mplus 5.1 (www.statmodel.com) we will fit a negative binomial regression model that includes one independent variable and mediator variables.

## Discussion

Our interdisciplinary research team will use a multi-pronged approach to explore the utility of OEP among seniors at high risk of future falls. The proposed trial may have important public health, economic, and mechanistic implications.

### Public health

The simple and proven exercise program (that is, the OEP) has already been implemented nationally in New Zealand. Therefore, if our study demonstrates the OEP is an efficacious and efficient (that is, cost-effective) secondary falls prevention program, our findings could be rolled out immediately by policy makers.

### Economic

The parallel economic evaluation is particularly important because, if the intervention proved to be cost-effective compared with standard of care, it would provide a strong argument for the OEP in the target population even at a time of fiscal restraint. We highlight that this intervention, the OEP, already has manuals, websites, and educational material ready for a ‘turn-key’ operation.

### Mechanistic

Better understanding of the primary mechanisms underlying the OEP (that is, our tertiary research objective) would increase our capacity to refine and develop novel interventions for secondary falls prevention for the aging population. If improved executive functions prove to play a significant role in falls reduction, it would be a major contribution to knowledge in this field.

## Trial status

As of 1 December 2014 we have obtained ethical approval, have registered the trial and we have successfully recruited 227 participants. We will aim to complete recruitment by 2017. One hundred and fifty four patients have completed 6-month follow-up, 133 have completed 12-month follow-up and 26 participants have dropped out. The median number of participation days for individuals who dropped out of the study was 103.5.

## Abbreviations

ABC: Activities-Specific Balance Confidence
EQ-5D-3L: Euro-Qol 5D three level version
ICER: Incremental cost-effective ratio
MMSE: Mini-Mental State Examination
MoCA: Montreal Cognitive Assessment
OEP: Otago Exercise Program
PPA: Physiological Profile Assessment
RCT: Randomized controlled trial
TUG: Timed Up and Go
